### 4.1.2 Study Date Range and Duration

Recruitment period: March 2025 – August 2026

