| Study Date Range and Duration
December 2024 – August 2026                                                                                                                                                                                                                                                                                                                  |
| Number of Study Sites
Yale New Haven Hospital                                                                                                                                                                                                                                                                                                                              |
| Primary Outcome Variables
We will use direct patient evaluation by pelvic floor therapists, a validated system usability survey to evaluate the ease of use of the web-based platform containing PFMT videos and monitor for adverse events.                                                                                                                               |
| Secondary and Exploratory Outcome Variables (if applicable)
Short Form 12 score, Cleveland Clinic Incontinence Score (CCIS), Patient Assessment of Constipation Symptoms (PAC-SYM), International Consultation on Incontinence Questionnaire Short Form (ICIQ-SF), and Pelvic Organ Prolapse Symptom Score (POP-SS) to assess improvement in symptoms and quality of life. |
| Study Population
Study population will include patients who have an indication for referral for pelvic floor rehabilitation (PFR).                                                                                                                                                                                                                                         |
| Number of Participants                                                                                                                                                                                                                                                                                                                                                        |

We plan to enroll 10-20 patients. This is a pilot study aimed at assessing feasibility, so this sample size is similar to other feasibility trials.

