## 1.2 Prior Experience (if applicable)

Our group conducted a study on patient reported barriers to completion of in-person PFR. We found the average time between referral and attendance of the first PFR session was 10 weeks. The two major barriers to completion included delay in available sessions (24%) and travel distance for attendance (20%). Furthermore, 35% of patients stated they would be amenable to a hybrid option using either telehealth or video-based strategies and 58% of patients would attend more sessions if there was a video-based option.

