## 4 Study Design

### 4.1.1 General Design Description

Patients will be enrolled during the clinic visit when they are initially referred for PFR. It will be explained that they are forgoing standard of care of all in-person pelvic floor rehabilitation and will complete the initial survey at this time. They will then have an introductory session with a pelvic floor therapist to assess their baseline function, which does not differ from the standard of care other than the pelvic floor therapist using a graded scoring system to assess exercise completion ability. This initial visit will be prioritized as the waitlist for pelvic floor rehabilitation can be up to 6 months. Then they will complete the 8 weeks of remote, self-directed video-based PFMT. At the midway point after completing 4 weeks of the remote, self-directed video based PFMT, patients will be contacted by a member of the research team to elicit feedback and complete a system usability scale to evaluate patient perspective of the online training program. After this period, they will have another in-person session with the same pelvic floor physical therapist to assess ability to complete exercises successfully with the same graded scoring system. They will then complete a system usability scale survey and repeat the initial surveys for QoL and symptom surveys within 2 weeks of the final in person pelvic floor therapist appointment.

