**6.11 Study Completion**

Recruitment will go from March 2025 with expected patient follow-up to last no longer than August 30 2026. Records will be retained for 3years from the end of the recruitment period with closure report submitted to the IRB on August 30th 2026.

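### Recruitment in 4.1.2 runs to August 2026, the month in which follow-up and study closure end, so participants enrolled after about 5 July 2026 cannot reach the final visit

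*Protocol*

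**What the plan says.** Three places in the protocol give calendar limits:

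- Synopsis, study date range: "December 2024 – August 2026".
- 4.1.2: "Recruitment period: March 2025 – August 2026".
- 6.11: recruitment starts in March 2025, with "expected patient follow-up to last no longer than August 30 2026", and the "closure report submitted to the IRB on August 30" of that year. Section 6.2 places the closure report after all research activities are complete.

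No earlier last-enrolment date is given.

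The participant's path is in 4.1.1. Entry is at referral: "Patients will be enrolled during the clinic visit when they are initially referred for PFR". An introductory therapist visit follows, and after it: "Then they will complete the 8 weeks of remote, self-directed video-based PFMT". A second in-person visit comes next. Completion surveys are due "within 2 weeks of the final in person pelvic floor therapist appointment" according to 4.1.1, but within 1 week according to 5.2 and 5.3.3.

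Section 4.1.1 says the introductory visit will be prioritised because the usual waitlist can reach 6 months. It does not say what wait remains. Section 1.2 reports, from the group's earlier study of in-person rehabilitation, that "the average time between referral and attendance of the first PFR session was 10 weeks".

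Section 5.4.6 excludes anyone who completes under 75% of the videos or misses either in-person visit. The enrolment target is 10 to 20 (4.3.1).

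**The concern.** Recruitment, last follow-up and closure share one end month, although every participant needs at least two months after entry. If sites recruit to the date in 4.1.2, the last people enrolled run out of calendar before their final visit.

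Section 5.4.6 makes no exception for people cut off by the study's end. They would leave the analysis just as if they had stopped the programme. In a feasibility study whose primary outcomes include video completion and the change in the therapist's graded evaluation, losses caused by the calendar would be mixed with losses caused by the intervention. With 10 to 20 participants, even one or two such losses matter. Enrolled patients also forgo standard all-in-person rehabilitation (4.1.1), so someone recruited too late does so without yielding a complete observation.

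**Working it through.** This is calendar arithmetic. The protocol gives no derivation of its dates, so there is no stated figure to reproduce.

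**Inputs**
- Last permitted follow-up: 30 August 2026 (6.11).
- Videos: 8 weeks between the first and final therapist visits (4.1.1).
- Completion surveys: 0 to 1 week (5.2, 5.3.3) or 0 to 2 weeks (4.1.1) after the final visit. These are maximum windows, so same-day completion is allowed.
- Wait from enrolment to first visit, w: not stated for this trial. I take w = 0 as the most favourable case and show other values as assumptions.
- Recruitment window: 1 March 2025 to 30 August 2026 = 547 days = 547/7 = 78.1 weeks. The first of March is assumed, since only the month is given.

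**Formulas**
- Latest enrolment that reaches the final visit = 30 August 2026 − (w + 8) weeks.
- Latest enrolment that also leaves the full 2-week survey window = 30 August 2026 − (w + 10) weeks.

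**Results with no wait (w = 0)**
- 8 weeks back: 5 July 2026. Anyone enrolled later cannot attend the final visit in time and is excluded by 5.4.6.
- 9 weeks back: 28 June 2026 (full 1-week survey window).
- 10 weeks back: 21 June 2026 (full 2-week survey window). People enrolled between 21 June and 5 July can finish the videos and attend the final visit. Their final SUS, SF-12 and symptom scores may be missing, but 5.4.6 does not exclude them for that.

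**Share of the window with no wait**
- 8/78.1 = 10.2% and 10/78.1 = 12.8%.
- With even accrual: 10 × 10.2% = 1.0 to 10 × 12.8% = 1.3 of 10 participants; 20 × 10.2% = 2.0 to 20 × 12.8% = 2.6 of 20.

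**Sensitivity to the unstated wait**

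| Assumed wait (weeks) | Latest enrolment to reach final visit | Latest enrolment with full 2-week survey window | Share of window |
|---|---|---|---|
| 0 | 5 July 2026 | 21 June 2026 | 10.2–12.8% |
| 2 | 21 June 2026 | 7 June 2026 | 12.8–15.4% |
| 4 | 7 June 2026 | 24 May 2026 | 15.4–17.9% |
| 10 | 26 April 2026 | 12 April 2026 | 23.0–25.6% |

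The last row applies the average wait from 1.2, which describes usual care and not this trial.

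**The case against.** The strongest reply is that August 2026 in 4.1.2 is simply a mislabelled study end. The section is headed as a study date range, the Synopsis uses the same heading for the whole study with the same end month, and 6.11 gives recruitment a start but no end, assigning August 2026 to follow-up. That reading is plausible. It does not remove the point: 4.1.2 would still state a wrong end of recruitment, and no last-enrolment date appears anywhere.

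A second reply is that a target of 10 to 20 over about 18 months may fill well before summer 2026, in which case nobody is lost. This stands. The participant counts hold only if enrolment is still open late and accrual is even, and the protocol supports neither assumption.

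A reader might also infer more than the documents support:

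- **That 19 to 20 weeks are unusable, making mid-April 2026 the true cut-off.** This applies the 10-week usual-care wait, whereas 4.1.1 says the trial's first visit will be prioritised. It is a scenario only.
- **That the minimum path is 9 to 10 weeks.** The survey windows are upper limits, so the minimum is 8 weeks.
- **That everyone who cannot complete all assessments is excluded.** Section 5.4.6 acts on missed visits and on under 75% of videos, not on missing surveys.
- **That late enrollees would be counted as non-adherent.** The protocol plans a complete-case analysis, so they would drop out of it.

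**Conclusion.** The concern holds in limited form. The end of recruitment in 4.1.2 cannot be reconciled with the Synopsis and 6.11, given a path of at least 8 weeks from first to final visit. This conclusion needs no assumption about waiting time.

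At its smallest it affects the last 8 weeks of recruitment through exclusion, and up to 2 further weeks through possible loss of the final surveys. The loss of roughly 1 of 10 or 2 to 3 of 20 participants is conditional on even accrual and late enrolment. A real wait for the first visit would enlarge it by an amount the protocol does not allow one to fix. This is a wrong stated date with a cheap correction, and it should be corrected while it can still govern enrolment.

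**What to change.** Choose one of two changes:

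1. In 4.1.2, replace the end of recruitment with a last-enrolment date at least 10 weeks plus the actual wait for the first visit before 30 August 2026. That means no later than 21 June 2026 with no wait, and earlier by whatever the prioritised wait proves to be.
2. Keep August 2026 as the end of recruitment and move the end of follow-up and the closure report later by the same interval. From an enrolment on 30 August 2026, 10 weeks leads to 8 November 2026, before any wait is added.

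In either case, align the Synopsis, 4.1.2 and 6.11, and state the wait on which the date rests. Settle the survey window too (2 weeks in 4.1.1, 1 week in 5.2 and 5.3.3); the 10-week figure uses the longer one. Section 6.11 counts record retention from the end of recruitment, so check that date as well.

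The cost is date edits in three places, with either a somewhat shorter recruitment window (10 of 78 weeks with no wait, more with one) or a later closure date.

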### 4.1.3 Number of Study Sites

Yale New Haven Hospital and the associated clinic sites

## 4.2 Outcome Variables

### 4.2.1 Primary Outcome Variables

SUS, percentage of video completion, change in the graded evaluation of exercises by pelvic floor therapist pre and post intervention, adverse events

### 4.2.2 Secondary and Exploratory Outcome Variables (if applicable)

Secondary outcomes will include the Short Form-12 (SF-12), along with one of the four appropriate symptom-focused surveys: 1) Cleveland Clinic Incontinence Score (CCIS), 2) Patient Assessment of Constipation Symptoms (PAC-SYM), 3) International Consultation on Incontinence Questionnaire Short Form (ICIQ-SF), and 4) Pelvic Organ Prolapse Symptom Score (POP-SS). These surveys are attached.

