### 4.3.2 Eligibility Criteria/Vulnerable Populations

Eligibility will be assessed by a member of the study team reviewing outpatient clinic visits to colorectal surgery and urogynecology clinics at Yale New Haven Hospital and its associated ancillary clinic sites.

In order to be eligible for inclusion in this study, an individual must meet all of the following criteria:

1. Diagnosis of one of the five following diagnoses with referral for PFR
  - a. Urinary incontinence
  - b. Pelvic pain
  - c. Fecal incontinence
  - d. Postpartum-related symptoms
  - e. Constipation
2. 18 years or older
3. English-speaking
4. Access to internet

Vulnerable populations: none

Exclusion criteria:

1. Unable to access web-based videos
2. Unable to speak English

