### 5.3.3 Study Visits (is applicable)

1. Initial clinic visit
  - a. SF-12
  - b. And one of the following surveys:
    - i. CCIS
    - ii. PAC-SYM
    - iii. ICIQ-SF
    - iv. POP-SS
2. In person visit with pelvic floor therapist (1 hour)
  - a. Introduction to PFMT clinical visit by a certified pelvic floor therapist
  - b. Graded evaluation of pelvic floor exercises on a scale of 1-3 ( 1= cannot replicate in any meaningful way, 2 = partially, 3 = fully perform)
3. Midway check-in with research team member (15 minutes)
  - a. Elicit feedback on self-direct video-based training
  - b. Completion of SUS
4. Completion in person visit clinical visit with pelvic floor therapist (1 hour)
  - a. Graded evaluation of pelvic floor exercises on a scale of 1-3 (1= cannot replicate in any meaningful way, 2 = partially, 3 = fully perform)
5. Completion survey within 1 week of seeing pelvic floor therapist
  - a. SF-12
  - b. And one of the following surveys:
    - i. CCIS
    - ii. PAC-SYM
    - iii. ICIQ-SF
    - iv. POP-SS
  - c. SUS

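### Pelvic pain is an entry diagnosis, but none of the four symptom surveys is named for pain and no rule links diagnosis to survey

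*Protocol*

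**What the plan says.** Protocol Section 4.3.2 requires a "Diagnosis of one of the five following diagnoses with referral for PFR". The five are urinary incontinence, pelvic pain, fecal incontinence, "Postpartum-related symptoms" and constipation.

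Section 4.2.2 sets the secondary outcomes as the SF-12 "along with one of the four appropriate symptom-focused surveys", and names them: CCIS, PAC-SYM, ICIQ-SF and POP-SS. Section 5.3.3 repeats the same closed list under "And one of the following surveys", once for the initial clinic visit and once for the completion survey. Section 4.1.1 says that the initial quality-of-life and symptom surveys are repeated at the end.

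Section 5.4.1 applies a paired t-test, before versus after treatment, to each of the four symptom scores and to the SF-12. Section 3.3 makes improvement in symptoms and quality of life the secondary objective, and Hypothesis B in Section 3.1 predicts both.

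**The concern.** The eligibility list and the survey list do not line up. Each patient must receive one of four surveys, yet one entry diagnosis, pelvic pain, has no survey bearing its name. The only guide to choosing is the word *appropriate* in Section 4.2.2.

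A pelvic-pain patient handled exactly as written is scored on continence, constipation or prolapse, and no symptom survey scores the complaint that led to referral. If the patient's pain improves, the planned symptom data need not show it. The score that is collected joins the paired test for that instrument, alongside patients for whom the instrument was meant.

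This cannot be left to the analysis stage. The survey is chosen and completed at the first clinic visit, and a baseline pain level that was never recorded cannot be recovered later.

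**Working it through.** No sample-size or power figure bears on this point. Section 5.4.2 sets 10-20 patients by analogy with other feasibility studies, so there is no figure of the plan's own to reproduce. The check is a cross-match of two lists.

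**Inputs.** Five diagnoses (Section 4.3.2); four surveys, one per patient (Sections 4.2.2 and 5.3.3); 10-20 patients (Section 4.3.1).

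**Match by name.** The protocol assigns no survey to any diagnosis, so names are the only basis for matching.

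| Entry diagnosis | Survey matching by name |
|---|---|
| Urinary incontinence | ICIQ-SF |
| Fecal incontinence | CCIS |
| Constipation | PAC-SYM |
| Postpartum-related symptoms | Depends on the presenting symptom; not stated |
| Pelvic pain | None |

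Three of five diagnoses have a survey matching by name. Three of four surveys match a listed diagnosis. The fourth, POP-SS, is named for prolapse, which is not a listed entry diagnosis and appears in the protocol only within that score's name.

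**Does another section repair this?**
- The survey-risk text in Section 2.3.1 describes the surveys as covering fecal incontinence, constipation and quality of life. It does not mention pain.
- Section 5.1.1 names only the SF-12, CCIS and PAC-SYM for the secondary analysis. Sections 5.4.1 and 5.4.3 add ICIQ-SF and POP-SS. None adds a pain measure.
- The surveys are said to be attached. An attachment would show the four questionnaires; it would not add a fifth to a list of four.
- Section 5.4.1 does not restrict each test to patients with the matching diagnosis.

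**Same survey at both times.** Section 4.1.1 implies it by having the initial surveys repeated. The completion entry in Section 5.3.3 lists all four again without tying the choice to baseline. A paired difference exists only if the instrument is the same at both times.

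**Size, for illustration.** Assume an even split, which the protocol neither states nor supports: 10/5 = 2 and 20/5 = 4, so 2-4 pelvic-pain patients, or 1/5 = 20%. With no case mix stated, the true share could lie anywhere from 0% to 100%.

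**The case against.** The strongest reply is that this is a small feasibility pilot. The primary outcomes in Section 4.2.1 are usability, video completion, graded exercise performance and adverse events, and none of them uses a symptom survey. Every patient also completes the SF-12 at both times, so the quality-of-life half of the secondary objective is covered. This stands, and it limits how serious the point is. It does not supply a symptom measure for an enrolled diagnosis.

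Four stronger readings are tempting, and the document does not support them:

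- *Postpartum patients are also without a survey, so 40% of the sample is unmatched.* "Postpartum-related symptoms" describes a setting rather than one symptom. Choosing the appropriate survey by presenting symptom is a natural reading, and POP-SS may be meant for these patients. The 40% also needs an even case mix that is not stated.
- *POP-SS has no use because prolapse is not an entry diagnosis.* Section 4.3.2 requires one of five diagnoses but does not exclude patients who also have prolapse symptoms.
- *Off-target scores start near zero and cannot improve.* This depends on item content and score ranges, which the protocol does not give.
- *A different survey may be used at completion.* Section 5.3.3 read alone leaves that open, but Section 4.1.1 points to the same one.

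**Conclusion.** The point holds in a narrow form. Pelvic pain is admitted, the survey list is closed, no survey on it is named for pain, and no rule connects diagnosis to survey. For a pelvic-pain patient the symptom part of the secondary objective cannot be answered as the plan stands, and an off-target score may enter one of the paired t-tests.

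This rests on one assumption: that each survey measures what its name says. The questionnaires are not shown, so whether any contains a pain item cannot be checked. The number of patients affected is unknown; 2-4 of 10-20 applies only under an even split.

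The sponsor should fix this, but it is not a fatal defect. It touches only the symptom half of a secondary objective.

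**What to change.** 1. In Sections 4.2.2 and 5.3.3, add a brief pain rating (for example 0-10) for pelvic-pain patients, at baseline and at completion.
2. In the same sections, fix the survey at enrolment by diagnosis: CCIS for fecal incontinence, PAC-SYM for constipation and ICIQ-SF for urinary incontinence. Assign postpartum patients by presenting symptom, including POP-SS where prolapse symptoms are present.
3. State in Section 5.3.3 that the survey used at baseline is the one used at completion, in line with Section 4.1.1.
4. Add the pain rating to the list of measures in Section 5.4.1, and bring the shorter list in Section 5.1.1 into agreement with it.

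The cost is an IRB amendment and one short item for some participants. It is best done before further baseline surveys are collected, because a missing baseline rating cannot be filled in afterwards.

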## 4.3 Study Population

The study population will include patients who have an indication for referral to PFR.

### 4.3.1 Number of Participants

A total of 10-20 patients will be enrolled in the study.

### 4.3.2 Eligibility Criteria/Vulnerable Populations

Eligibility will be assessed by a member of the study team reviewing outpatient clinic visits to colorectal surgery and urogynecology clinics at Yale New Haven Hospital and its associated ancillary clinic sites.

In order to be eligible for inclusion in this study, an individual must meet all of the following criteria:

1. Diagnosis of one of the five following diagnoses with referral for PFR
  - a. Urinary incontinence
  - b. Pelvic pain
  - c. Fecal incontinence
  - d. Postpartum-related symptoms
  - e. Constipation
2. 18 years or older
3. English-speaking
4. Access to internet

Vulnerable populations: none

Exclusion criteria:

1. Unable to access web-based videos
2. Unable to speak English

## 5 Study Methods/Procedures

### 5.1 Study Procedures

1. Initial survey completion at initial clinic visit
2. In person visit with pelvic floor physical therapist
3. 8 weeks of online video-based PFMT program
4. Midway check-in with research member and survey completion
5. Completion in person visit with pelvic floor therapist
6. Completion surveys after 8 weeks of video-based PFMT

#### 5.1.1 Data Collection

The survey information will be collected by a trained survey either in person or filled out independently by the study participant using a Yale-licensed Qualtrics platform. If there are technical difficulties, a paper-based version of the assessment tool will be substituted and later inputted. This data and the clinical data will be collected from the electronic medical records (e.g., Epic® chart reviews) and will be securely stored in the HIPAA compliant RedCap database. The assessment by the pelvic floor therapist will also be secured inputted into the RedCap database.

At the completion of the study period, we will compare the assessment of PFMT adequacy as assessed by the pelvic floor therapists, usability of the video-based application, and any adverse events as our primary outcome for feasibility and safety. We will analyze the change in the SF-12 score, CCIS, PAC-SYM, pre and post intervention to evaluate any change as our secondary outcome evaluating for efficacy of video-based PFMT.

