# 1 Background/Literature Review

## 1.1 Background

Pelvic floor rehabilitation (PFR) is a group of therapeutic techniques used to help patients with pelvic floor dysfunction, such as urinary incontinence or fecal incontinence. The exercises commonly use in PFR include pelvic floor muscle therapy (PFMT) with biofeedback training, rectal balloon training or electrical stimulation. Together, these techniques aim to improve the strength, tone and endurance of the pelvic floor musculature and sphincter complex. For fecal incontinence, they have shown to decrease symptoms ranging between 50-80%. A meta-analysis looking at 18 trials utilizing PFMT for urinary incontinence found an improvement in symptoms in all studies.

Despite PFMT being shown to be efficacious for numerous different pelvic floor dysfunction disorders, less than 50% of patients referred are compliant with the recommend duration of treatment. Previous studies found that inconvenience, cost, lack of knowledge and discomfort around the concept of PFMT are all reasons why patients may have poor compliance. Patients have shown a positive reception to telehealth-based PFMT visits. It is not known if a hybrid approach to PFMT including both in-person and video-based training videos may help to alleviate some of these barriers while providing the same adequate amount of guidance, improvement in symptoms and QoL for patients. Thus, the purpose of this study is to evaluate the feasibility and acceptability of a web-accessible 8-week video-based PFMT for pelvic floor disorders.

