#### **5.4.5 Interim Analysis (if applicable)**

#### **5.4.6 Handling of Missing Data**

Patients who complete less than 75% of the videos or do not attend both initial and final in person pelvic floor therapy visit will be excluded from the study. A complete case analysis will be performed for patients who have completed between 75-100% of the videos.

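### Video completion is a primary outcome and sets the 75% exclusion, but the protocol states neither its source nor its denominator and leaves it out of the primary analysis

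*Protocol*

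**What the plan says.** Section 4.2.1 gives the primary outcomes as "SUS, percentage of video completion, change in the graded evaluation of exercises by pelvic floor therapist pre and post intervention, adverse events".

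Section 5.4.6 uses the same variable as a filter. It excludes "Patients who complete less than 75% of the videos", together with anyone who misses the initial or final in-person visit, and adds: "A complete case analysis will be performed for patients who have completed between 75-100% of the videos".

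Section 5.1.1 describes three kinds of data: surveys (Qualtrics, or paper as a fallback), clinical data from the medical record, and the therapist's grading, of which it says "The assessment by the pelvic floor therapist will also be secured inputted into the RedCap database". For the week-4 contact, 5.3.3 lists two items: the System Usability Scale (SUS) and "Elicit feedback on self-direct video-based training". Section 5.2 says the videos are on a website and gives its address, with no mention of tracking.

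**The concern.** One variable does two jobs. It is an endpoint of a study whose purpose is feasibility, and it selects the patients in whom the other endpoints are assessed. Both jobs need a per-participant value with a known source and a fixed denominator, and the protocol provides neither.

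The timing makes this more than missing detail. The videos are used at home, unsupervised, for eight weeks. If nothing ties viewing to a participant during that time, what remains is whatever people can recall. A later analysis document can define how to summarise completion, but it cannot supply values that were not recorded.

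There is a second problem even if capture is perfect. Under 5.4.6, patients with low completion leave the study data, so the completion outcome can no longer show low completion.

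**Working it through.** The protocol gives no figure for completion and no power calculation, so there is nothing to reproduce. The check is a comparison of sections, followed by two pieces of arithmetic.

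**Step 1. Where completion is used, and where it could be captured or analysed**

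| Protocol section | Content bearing on completion |
|---|---|
| 4.2.1 Primary Outcome Variables | Named as primary |
| 5.4.6 Handling of Missing Data | Exclusion below 75%; analysis set 75-100% |
| Synopsis, primary outcomes | Therapist evaluation, usability survey, adverse events; completion absent |
| Synopsis, Study Schedule | Week-4 contact is for checking progress; no data item named |
| 4.1.1 General Design | Week-4 feedback and SUS; no viewing record |
| 5.1 Study Procedures | Six steps; none records viewing |
| 5.1.1 Data Collection | Surveys, medical record, therapist grading; its primary-outcome sentence omits completion |
| 5.2 Study Schedule | Website address only |
| 5.3.3 Study Visits | Surveys, grading, feedback, SUS |
| 5.4.1 Statistical Design | Seven paired measures; completion absent |
| 5.4.3 Planned Analyses | Share who learned the exercises, adverse events, usability, grading; completion absent |

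Two sections use the variable. None states its source. The number of videos assigned and what counts as a completed video are also not stated, so the 75% has no defined denominator.

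**Step 2. Completion among those analysed**

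Let n patients be enrolled and k be retained under 5.4.6. Each retained patient has completion between 75% and 100%, so their mean lies in that interval for every k. The mean in all enrolled is bounded below only by 75% × k/n, reached when the retained are all at 75% and the others at zero. The protocol gives no expected k, so the values below are assumptions across the range, with n = 20:

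| k retained | Mean among analysed | Lowest possible mean in all enrolled |
|---|---|---|
| 20 | at least 75% | 75 × 20/20 = 75% |
| 15 | at least 75% | 75 × 15/20 = 56.25% |
| 10 | at least 75% | 75 × 10/20 = 37.5% |
| 5 | at least 75% | 75 × 5/20 = 18.75% |

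The figure among those analysed cannot tell these cases apart.

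**Step 3. Sensitivity of the cut to one patient**

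Enrolment is 10-20 (4.3.1). One patient classified on the wrong side of 75% changes the analysed share by 1/20 = 5 percentage points to 1/10 = 10 percentage points. With the source and denominator left open, such a patient is easy to produce.

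**The case against.** **Silence is not absence.** The synopsis describes a midpoint contact to check progress, and the website may log views. Both points stand. A reader might infer that completion is unmeasured, or that one primary outcome will not exist; the protocol supports only that no measurement is specified. The midpoint contact does not close the gap, because no data item is attached to it and it cannot cover weeks 5 to 8.

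**The SAP may deal with it.** How a percentage is tabulated is commonly left to the SAP, which is not shown, and 5.4.6 does use the variable. That is fair as to tabulation. It does not cover the source of a primary outcome, nor the disagreement between 4.2.1 and the three places that describe the primary outcome or analysis without it.

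**Stronger readings that do not hold.**
- A reader might put a number on inflation from end-of-study recall. The protocol does not say that recall will be used, and any size of over-reporting would be invented.
- A reader might take the Background statement that "less than 50% of patients referred are compliant with the recommend duration of treatment" to mean that about half the participants would have no value. That statement concerns referred patients and the recommended duration of treatment, not attendance at one final visit for which 6.1 pays $25. Patients who miss that visit are in any case excluded whatever their video count, so a missing value for them affects the completion outcome but not the analysis set.
- A reader might infer that the whole feasibility result is biased upward. Over-reporting would raise completion itself. It would also bring patients with little exposure into the analysed set, which could lower the therapist's grades.

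**Conclusion.** The point holds as a gap in specification and an internal inconsistency. A primary outcome that also defines the analysis set has no stated source and no stated denominator, and it is missing from the synopsis outcome list, from the outcome sentence in 5.1.1 and from the planned primary analysis in 5.4.3. Separately, 5.4.6 forces completion among those analysed to be at least 75%, so as written the outcome cannot reveal poor completion.

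The size that can be stated without outside assumptions is the 75% floor and the 5 to 10 percentage points per misclassified patient. The conclusion rests on reading 5.4.6 literally, with excluded patients contributing to no outcome, and on there being no capture arrangement outside this protocol. If the site already logs views by participant, the remedy reduces to writing that down and reporting completion in everyone enrolled. It should be settled before further patients begin the videos, because the data may not be recoverable afterwards.

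**What to change.** - In 5.1.1 and 5.2, name one prospective, per-participant source: individual view logs if the website supports them, otherwise a brief weekly Qualtrics item. State the denominator (videos assigned) and what counts as a completed video.
- Store the values in REDCap under the study identification number, as the protocol does for its other research data, and keep them up to last contact for participants who stop.
- In 5.4.6, state that the 75% figure applies only to that source.
- In 5.4.3, add a report of completion in all enrolled patients.
- Bring the synopsis outcome list, the outcome sentence in 5.1.1 and the primary analysis in 5.4.3 into line with 4.2.1.

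The cost is an IRB amendment (6.10) and, if the weekly item is used, a small participant burden. The documents do not say whether the site can produce individual logs, so that must be checked first. If it can, the logs must be moved into REDCap, because that is where the protocol places study data.
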